### Outcome Measurement

For an evaluation of the primary and secondary outcome measures, the participants are required to complete 2 questionnaires, the Total Ocular Symptom Score (TOSS) and the Total Nasal Symptom Score (TNSS) [19]. These questionnaires will be completed at the beginning of each of the 4 treatment sessions (from week 2 to week 5) and in weeks 8, 12, and 16 during each follow-up session. During the follow-up process, the participants need to independently record their Rhinitis Control Assessment Test (RCAT) scores weekly [20]. In addition, the participants will be asked to complete diaries throughout the trial. The primary outcome is the recurrence rate 3 months after discontinuation. Once the treatment-effective participants discontinue the medication (RCAT score less than 21 points), they will immediately enter the follow-up period. If a relapse occurs, the relapse time will be promptly recorded, and the follow-up will conclude. Otherwise, the participants will continue to be monitored until 3 months after discontinuation of medication. RCAT is one of the most commonly used rhinitis control scales, and its reliability, validity, and responsiveness have been widely verified [21,22]. A score of 21 corresponds to the validated RCAT score of 25, which determines the controlled state of rhinitis. When RACT ≤21, it indicates an uncontrolled state of AR and the starting point for treatment [23]. RCAT is a simple self-rating scale that allows patients to assess their AR control at home and helps assess the success of long-term repeated treatment interventions [20,24]. TNSS evaluates 4 nasal symptoms: nasal obstruction, sneezing, rhinorrhea, and nasal itch. The symptoms are self-assessed and recorded by participants using a 5-point scale (0=no symptoms; 1=mild symptoms; 2=moderate symptoms; 3=severe symptoms; 4=very severe symptoms) [23]. TNSS scores range from 0 to 16, with low scores indicating lighter nasal symptoms. TOSS assesses eye symptoms, including redness, itchiness, and tearing. Each symptom is assessed on a scale between 0 and 3 (absent to most severe), with a total score from 0 to 9 [19,25]. The score represents an average for both eyes. The secondary outcomes include (1) changes in TNSS and TOSS score from baseline to weeks 8, 12, and 16; (2) response to interventions, defined as participants with a change in TNSS score of ≥0.5 from baseline; (3) and serum levels of tumor necrosis factor-alpha (TNF-α), IFN-γ, IL-4, IL-17, and IgE, measured by enzyme-linked immunosorbent assay according to the manufacturer's protocol (Bio-Techne).

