### Statistical Analyses

Intentional therapeutic analysis will be adopted, with missing values estimated using the last observation carried forward method. Mean and SD (for continuous variables that obey normal distribution), median and quartile (for continuous variables that do not obey normal distribution), and frequency and percentage (for classified variables) will be used for the statistical description. According to the numerical characteristics of the variables, quantitative data such as age, height, and weight of the 2 groups will be compared using a *t* test or the Wilcoxon rank sum test. The chi-square test or Fisher exact probability method will be used to compare qualitative variables, such as sex and nationality between the 2 groups. Cox regression analysis will be carried out with recurrence outcome and time of first recurrence as dependent variables, and the differences in survival curves between both groups will be compared. SPSS software (version 23.0; IBM Corp) will be used for statistical analysis. A 2-sided test will be used for all statistical inferences, and *P*<.05 will be considered statistically significant.

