The purpose of this trial is to reduce the recurrence of rhinitis, relieve symptoms, and achieve clinical benefit by using ACE as a nondrug therapy. Previous articles about ACE for the treatment of AR lack placebo-controlled, high-quality research [26]. Therefore, it is necessary to provide high-quality research in this domain. We designed this RCT to examine whether ACE treatment decreases recurrence and improves symptoms such as sneezing, clear watery nasal discharge, itchy nose, and nasal congestion in patients with AR. The main limitation of this study is its single-blind design. Another potential limitation is the possibility of patient attrition due to the requirement of undergoing treatment over 4 weeks, totaling 4 times. Another limitation is our inability to design double-blind trials due to the material and design of the embedding needles. Moving forward, our aim is to develop improved embedding needles that align more closely with the requirements of double-blind testing, thereby enhancing the international promotion of this therapy. The strengths of this study include the use of a randomized controlled design, with all patients being followed up. Both subjective and objective data will be collected in this study to examine the effectiveness of ACE in treating AR. Another advantage is that it focuses on decreasing recurrence. The results of this study could improve the treatment outcomes of patients with AR. We posit that this research will provide important insights into the efficacy of ACE treatment for AR and generate robust data for the foundation of future research in this field.

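### Follow-up stops at relapse and missing values are filled by LOCF, so the week 8, 12 and 16 TNSS and TOSS changes largely miss the worsening that relapse brings

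*Protocol article*

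**What the plan says.** All the relevant text is in the protocol article.

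- **Stop rule (Outcome Measurement).** "If a relapse occurs, the relapse time will be promptly recorded, and the follow-up will conclude". For everyone else: "Otherwise, the participants will continue to be monitored until 3 months after discontinuation of medication".
- **Symptom scores (Outcome Measurement).** After treatment, TNSS and TOSS are taken "in weeks 8, 12, and 16 during each follow-up session". The first secondary outcome is "changes in TNSS and TOSS score from baseline to weeks 8, 12, and 16". No TNSS or TOSS assessment at the time of relapse is mentioned.
- **Relapse monitoring (Outcome Measurement).** During follow-up, "the participants need to independently record their Rhinitis Control Assessment Test (RCAT) scores weekly". A relapse can therefore come to light between two TNSS/TOSS visits.
- **Missing data (Statistical Analyses).** "Intentional therapeutic analysis will be adopted, with missing values estimated using the last observation carried forward method". No outcome is exempted.
- **Recurrence.** Outcome Measurement defines the primary outcome as a 3-month rate. The only analysis that Statistical Analyses ties to recurrence is Cox regression on time to first recurrence, with a comparison of survival curves.
- **Discussion.** Among the strengths listed is a randomised design "with all patients being followed up".

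Outcome Measurement describes entry into follow-up only for participants in whom treatment worked. It is therefore also unclear whether the others have scores at weeks 8 to 16.

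**The concern.** The stop rule and the LOCF rule work against the secondary outcome. A participant who relapses at week 9 has no TNSS or TOSS at weeks 12 and 16, and the reason is that the participant got worse. LOCF then supplies the latest earlier score, usually one taken before the relapse. The arm with more relapses receives more of these favourable substitutes, so the analysis loses the symptom difference that the trial's primary hypothesis predicts.

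This is more than a detail that an analysis plan could settle later, because scores that were never collected cannot be recovered by analysis. The article says that recruitment is under way and that the study ends in February 2026.

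There is a second, conditional issue. The LOCF statement is general and the primary outcome is worded as a rate. If LOCF were applied to recurrence status, anyone who left follow-up without a relapse would be carried to 3 months as recurrence-free.

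**Working it through.** The article gives no figure on this point to reproduce, and no recurrence rates or expected TNSS values. The numbers below are an illustration on stated assumptions.

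**Assumptions for TNSS**
- TNSS is 4 while controlled and 9 from relapse onward (the article's scale runs from 0 to 16).
- Baseline means are equal in the two arms, so a difference in change equals a difference in score.
- There is no treatment effect other than through relapse.
- Time to relapse is exponential, with 12-week relapse probability p.
- Week 5, the last treatment session, is taken as time 0, so weeks 8, 12 and 16 are 3, 7 and 11 weeks later.

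**If relapsed participants stay in follow-up.** The proportion relapsed by week 16 is 1 − (1 − p)^(11/12).
- p = 0.30: 27.9%, mean TNSS 4 + 5 × 0.279 = 5.39
- p = 0.50: 47.0%, mean TNSS 4 + 5 × 0.470 = 6.35
- Difference, sham minus ACE: 0.96

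**If follow-up stops and no TNSS is taken at relapse.** Every relapsed participant carries forward a 4. Both means are 4.0 and the difference is 0.

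**If a relapse found in a visit week has a TNSS recorded.** Only relapses detected in weeks 3, 7 or 11 after time 0 contribute a 9. Their proportion is the sum over w = 3, 7, 11 of (1 − p)^((w−1)/12) − (1 − p)^(w/12).
- p = 0.30: 0.0276 + 0.0245 + 0.0218 = 0.0739, mean 4.37
- p = 0.50: 0.0500 + 0.0397 + 0.0315 = 0.1212, mean 4.61
- Difference: 5 × (0.1212 − 0.0739) = 0.24

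**Range over assumed relapse rates, week-16 difference**

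| Relapse, ACE vs sham | Follow-up continued | Stop + LOCF, no score at relapse | Stop + LOCF, visit-week relapses scored |
|---|---|---|---|
| 45% vs 50% | 0.24 | 0 | 0.06 |
| 30% vs 50% | 0.96 | 0 | 0.24 |
| 20% vs 60% | 1.92 | 0 | 0.47 |

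Even in the milder case about three quarters of the difference due to relapse is lost.

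**Recurrence, only if LOCF is applied to the 3-month rate.** With exponential recurrence and dropout, λ = −ln(1 − p) and μ = −ln(1 − d) over the period. The reported rate is λ/(λ + μ) × [1 − exp(−(λ + μ))]. Take d = 20% in both arms as an assumption. The 20% in Sample Size Calculation is explained by ineffective treatment and is not a clean dropout rate.
- p = 0.50: 0.693/0.916 × 0.600 = 45.4%
- p = 0.45: 0.598/0.821 × 0.560 = 40.8%

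Both rates are understated, and a true 5-point difference is reported as 4.6 points. If dropouts are instead censored and dropout is unrelated to recurrence, this bias does not arise.

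**The case against.** Four counter-arguments deserve weight.

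1. *The stop rule may concern the primary outcome only.* It stands within the description of recurrence, TNSS and TOSS have their own schedule, and the Discussion says that everyone is followed up. This is a possible intention, but the sentence ends follow-up without qualification and nothing limits it to recurrence. The Discussion remark conflicts with it and does not override it.

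2. *A reader might infer that every carried score precedes relapse and that the symptom difference vanishes.* The documents do not support that. A relapse found in a visit week may have a TNSS to carry forward. LOCF would also leave intact any difference already present at the end of treatment. Relief medication is allowed in follow-up, so relapsed scores need not stay high. The zero is a worst case.

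3. *A reader might infer that dropouts are counted as recurrence-free in the primary analysis.* The article does not say so. The one analysis named for recurrence is Cox regression, where dropouts are ordinarily censored. What stands is that an unrestricted LOCF rule sits beside a rate endpoint, and the article does not say which treatment governs. Nor does it give grounds to expect unequal dropout: both arms have the same visits, needle procedure and loratadine. A spurious difference in recurrence between arms cannot be claimed.

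4. *The bias runs toward no difference.* For the relapse mechanism this is correct. It hides a benefit and does not manufacture one. That lowers the severity but does not make the secondary outcome interpretable.

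**Conclusion.** The point holds for TNSS and TOSS. As written, scores at weeks 8, 12 and 16 are missing because of relapse and are filled with mostly pre-relapse values, which favours the arm with more relapses. The direction needs only that relapse raises symptom scores. The size depends on assumed values: a week-16 TNSS difference of 0.24 to 1.92 points falls to between 0 and 0.47, and the central example falls from 0.96 to 0 or 0.24. These figures assume no treatment effect outside relapse and a constant relapse score.

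For recurrence the conclusion is conditional. LOCF on the 3-month rate would conflict with the usual censoring in the planned Cox analysis, and the article should exclude it expressly. It does not establish that the primary result will be biased.

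This should be fixed. It affects secondary outcomes, the remedy is cheap, and delay loses data for good.

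**What to change.** - **Outcome Measurement:** state that relapse ends follow-up for the recurrence endpoint only, and that TNSS and TOSS continue at weeks 8, 12 and 16 for all randomised participants, including those who relapsed or did not respond. Bring the Discussion's statement about follow-up into line.
- **Statistical Analyses, TNSS and TOSS:** replace LOCF ("with missing values estimated using the last observation carried forward method") with a repeated-measures mixed model adjusted for the baseline score. The model alone is not enough. Relapse is tracked through weekly RCAT, which a TNSS model does not contain, so continued collection is the essential part.
- **Statistical Analyses, recurrence:** state that LOCF does not apply. Censor dropouts at their last weekly RCAT and take the 3-month rate from the Kaplan-Meier estimate. This rests on dropout being unrelated to recurrence, which should be said.

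The cost is revised wording and a slight burden of at most three already-scheduled TNSS/TOSS assessments for each relapsed participant. No treatment rule changes. Scores already lost for participants who relapsed before the change stay missing, and their number by arm should be reported.

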
### Serum Acquisition

The participants’ venous blood samples will be collected using blood collection tubes, symmetrically placed in the centrifuge sample bin, and covered. The rotation speed will be set to 4000 rpm, and the centrifuge time will be 10 minutes. The machine will be turned off after centrifugation, the sample bin opened, the sample carefully taken out, and the separation of the sample observed. If it is unsatisfactory, the sample will be centrifuged again. The serum will be carefully sucked from the upper layer with a 1-ml pipette, moved to an Eppendorf tube, and stored in a refrigerator at –80 °C degrees for inspection. Serum TNF-a, INF- γ, IL-17, IL-4, and IgE levels will be measured using enzyme-linked immunosorbent assay [26].

### Basic Characteristic Variables

Demographics such as age, sex, height, body mass, and BMI will be obtained. Vital signs including temperature, blood pressure, heart rate, and breathing will also be measured. Data on patient medical history, family history, risk factors, and dietary history will be collected.

### Statistical Analyses

Intentional therapeutic analysis will be adopted, with missing values estimated using the last observation carried forward method. Mean and SD (for continuous variables that obey normal distribution), median and quartile (for continuous variables that do not obey normal distribution), and frequency and percentage (for classified variables) will be used for the statistical description. According to the numerical characteristics of the variables, quantitative data such as age, height, and weight of the 2 groups will be compared using a *t* test or the Wilcoxon rank sum test. The chi-square test or Fisher exact probability method will be used to compare qualitative variables, such as sex and nationality between the 2 groups. Cox regression analysis will be carried out with recurrence outcome and time of first recurrence as dependent variables, and the differences in survival curves between both groups will be compared. SPSS software (version 23.0; IBM Corp) will be used for statistical analysis. A 2-sided test will be used for all statistical inferences, and *P*<.05 will be considered statistically significant.

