### Sample Size Calculation

Our preliminary study [28] indicated that the 3-month recurrence rate of the ACE group should be at least 5% lower than that of the Sham ACE group to be clinically significant. Using α=0.025 (unilateral), β=0.2, △=5%, and K=1, the sample size was estimated based on the comparison of two sample rates in the optimization test. The sample size in each group was calculated to be 52. Since the effectiveness of any treatment was not 100%, patients with ineffective treatment in this study could not be included in the assessment of recurrence, so the loss of follow-up rate in this study was 20%, which amounted to 126 cases. The \following equation is used to calculate the sample size, which refers to the estimated number of patients to be enrolled in the study:

[figure not shown]

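### The only tests the article names for quantitative data are unadjusted; adjusting TNSS and TOSS for the baseline score already collected would give a more precise comparison at almost no cost

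*Protocol article*

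**What the plan says.** Under Outcome Measurement, the first secondary outcome is "changes in TNSS and TOSS score from baseline to weeks 8, 12, and 16". On timing, the same section says "These questionnaires will be completed at the beginning of each of the 4 treatment sessions (from week 2 to week 5" and adds the three follow-up visits at weeks 8, 12 and 16. The questionnaire completed before the first session is therefore a pre-treatment score, and defining the outcome as a change presupposes one.

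The Statistical Analyses section chooses tests by type of variable. For continuous variables it states that "quantitative data such as age, height, and weight of the 2 groups will be compared using a *t* test or the Wilcoxon rank sum test". Qualitative variables get a chi-square or Fisher exact test. The one regression model is reserved for the primary outcome: "Cox regression analysis will be carried out with recurrence outcome and time of first recurrence as dependent variables". On the significance level, "A 2-sided test will be used for all statistical inferences", with a threshold of 0.05. The section does not mention TNSS, TOSS or adjustment for baseline.

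**The concern.** TNSS and TOSS change are quantitative data in two groups, and the t test and the rank sum test are the only methods offered for such data. An analyst who follows the section literally would apply one of them to the change scores, and neither uses the baseline score as a covariate.

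Subtracting the baseline is not the same as adjusting for it. The change score fixes the slope of follow-up on baseline at 1, whereas the true slope is usually smaller. The entry criteria require current symptoms but set no TNSS range, so baseline scores may spread widely over the 0 to 16 scale. Patients who start high tend to fall further through regression to the mean. Two things follow: the confidence interval is wider than the data require, and part of any chance baseline difference between the arms stays in the estimate from this one trial.

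The Discussion lists symptom relief among the trial's purposes, and these two scores are its main evidence on that.

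**Working it through.** **The plan's own figures.** The article gives no power, SD or correlation for TNSS or TOSS, so there is no figure to reproduce on this point. The sample size of 52 per group, raised to 126 in total, was set for recurrence and does not bear on it. It serves here only to give the arm size, 126/2 = 63.

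**Inputs.**
- Two-sided alpha 0.05 (Statistical Analyses).
- 63 per arm (Sample Size Calculation).
- Correlation rho between baseline and follow-up score: not in the document. Assumed, range 0.3 to 0.8.
- Equal SD at baseline and follow-up: assumed.

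**Variance.** For a comparison of Y − bX, with Y the follow-up score and X the baseline score, the per-patient variance is SD² × (1 + b² − 2b·rho).
- Change score, b = 1: 2(1 − rho) × SD².
- ANCOVA, b = rho, which minimises the expression: (1 − rho²) × SD².
- Ratio of ANCOVA to change score: (1 − rho²) / [2(1 − rho)] = (1 + rho)/2.

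**Power.** Suppose the true difference gives the change-score t test 80% power. Its standardised size is 1.960 + 0.842 = 2.802. Under ANCOVA this becomes 2.802/√ratio, and power is approximately Φ(2.802/√ratio − 1.960). At rho 0.5, for example, 2.802/√0.75 = 3.235, 3.235 − 1.960 = 1.275, and Φ(1.275) = 0.899. The reverse calculation sets ANCOVA at 80% and multiplies by √ratio.

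| rho | Change-score variance (SD²) | ANCOVA variance (SD²) | Ratio | ANCOVA power when change score has 80% | Change-score power when ANCOVA has 80% |
|---|---|---|---|---|---|
| 0.3 | 1.40 | 0.91 | 0.65 | 93.5% | 61.7% |
| 0.5 | 1.00 | 0.75 | 0.75 | 89.9% | 67.9% |
| 0.7 | 0.60 | 0.51 | 0.85 | 86.0% | 73.3% |
| 0.8 | 0.40 | 0.36 | 0.90 | 84.0% | 75.7% |

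Because the effect is calibrated to 80% power, these figures are practically the same at 52 or 63 per arm.

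**A fixed effect, for illustration.** With an assumed true difference of 0.5 SD, rho 0.5 and 63 per arm, power is 79.5% for the change score and 89.5% for ANCOVA (noncentral t).

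**Chance imbalance.** If the arms happen to differ by 0.2 SD at baseline, the change-score estimate moves by (1 − rho) × 0.2 SD: 0.14, 0.10, 0.06 and 0.04 SD at rho 0.3, 0.5, 0.7 and 0.8. The movement averages to zero over randomisations.

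**Limits.** The formulas are for the t test; the rank sum option was not calculated separately. They take the scores as given and leave aside how missing ones are filled.

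**The case against.** The strongest reply is that the plan never makes this choice. Age, height and weight are baseline characteristics, the parallel sentence on qualitative variables cites sex and nationality, and the section before the analysis (Basic Characteristic Variables) lists such characteristics. On that reading the sentence describes only the baseline comparison, and the model for TNSS and TOSS is left to a fuller protocol or analysis plan that is not shown. An article's silence on that would be no fault.

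Much of this stands. A reader might infer that the plan prescribes a t test for TNSS and TOSS change; no sentence says so. What remains is that the rule is worded for quantitative data in general, with the demographic variables as examples, and no other method for a continuous outcome is stated. The point therefore concerns where the written rule leads, not a missing detail.

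A reader might also infer that the unadjusted result would be biased. It would not: with 1:1 randomisation the change-score comparison is unbiased, and chance imbalance costs precision only. It is also fair to say that rho is unknown, that the gain is small when rho is high, and that the trial was not powered on these scores, so no stated design figure fails.

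**Conclusion.** The point holds as a matter of efficiency. The only tests named for quantitative data are unadjusted, and applied as written to TNSS and TOSS change they discard precision that the collected baseline scores could supply. With equal SDs and rho between 0.3 and 0.8, adjustment reduces the variance by 35% to 10%. In power, that is a gain of about 13 to 4 points from a starting point of 80%. The direction holds for any rho below 1, apart from the one degree of freedom spent; the size rests on a correlation that the document does not give.

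The point does not show an invalid or biased analysis, nor that the authors have settled on unadjusted tests for these outcomes. It is confined to secondary outcomes and leaves the primary Cox analysis of recurrence untouched. It is a worthwhile and nearly free improvement, not a flaw that threatens the trial's conclusion.

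**What to change.** In Statistical Analyses, add one sentence: TNSS and TOSS at weeks 8, 12 and 16 are each compared between groups by a linear model with treatment group and the patient's own baseline score as covariates, and the adjusted mean difference is reported with its 95% CI. Restrict the t test and Wilcoxon sentence to describing baseline variables.

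The outcome definition can stay as it is: with baseline in the model, the estimated group difference is the same whether the response is the score or its change. If a fuller plan already specifies baseline adjustment, the same sentence brings the article into line with it.

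The cost is one sentence and one degree of freedom per model. No new data, visits or patients are needed, and the SPSS version already named fits the model.
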